# An evaluation of a combined psychological and parenting intervention for HIV-positive women depressed in the perinatal period, to enhance child development and reduce maternal depression: study protocol for the Insika Yomama cluster randomised controlled trial

**DOI:** 10.1186/s13063-021-05672-0

**Published:** 2021-12-13

**Keywords:** Perinatal depression, Behavioural activation, HIV, Parenting, Child development, Lay counsellors

## Abstract

**Background:**

The combination of poverty, HIV and depression in the perinatal period represents a major public health challenge in many Southern African countries. In some areas, up to a third of HIV-positive women experience perinatal depression. Perinatal depression is associated with negative effects on parenting and key domains of child development including cognitive, behavioural and growth, especially in socio-economically disadvantaged communities. Several studies have documented the benefits of psychological interventions for perinatal depression in low- and middle-income countries, but none have evaluated an integrated psychological and parenting intervention for HIV-positive women using task-sharing. This randomised controlled trial aims to evaluate the effect of a home-based intervention, combining a psychological treatment for depression and a parenting programme for perinatally depressed HIV-positive women.

**Methods:**

This study is a cluster randomised controlled trial, consisting of 48–60 geospatial clusters. A total of 528 pregnant HIV-positive women aged ≥ 16 years who meet the criteria for depression on the Edinburgh Postnatal Depression Scale (EPDS, score ≥ 9)) are recruited from antenatal clinics in rural KwaZulu-Natal, South Africa. The geospatial clusters are randomised on an allocation ratio of 1:1 to either the intervention or Enhanced Standard of Care (ESoC). The intervention group receives 10 home-based counselling sessions by a lay counsellor (4 antenatal and 6 postnatal sessions) and a booster session at 16 months. The intervention combines behavioural activation for depression with a parenting programme, adapted from the UNICEF/WHO Care for Child Development programme. The ESoC group receives two antenatal and two postnatal counselling support and advice telephone calls.

In addition, measures have been taken to enhance the routine standard of care.

The co-primary outcomes are child cognitive development at 24 months assessed on the cognitive subscale of the Bayley Scales of Infant Development-Third Edition and maternal depression at 12 months measured by the EPDS.

**Analysis:**

The primary analysis will be a modified intention-to-treat analysis. The primary outcomes will be analysed using mixed-effects linear regression.

**Discussion:**

If this treatment is successful, policymakers could use this model of mental healthcare delivered by lay counsellors within HIV treatment programmes to provide more comprehensive services for families affected by HIV.

**Trial registration:**

ISRCTN registry #11284870 (14/11/2017) and SANCTR DOH-27-102020-9097 (17/11/2017).

## Introduction

### Background and rationale {6a}

#### Perinatal depression in the context of HIV

Perinatal depression is common amongst HIV-positive women globally and a major public health challenge [1, 2]. A 2015 systematic review of African studies of perinatal depression amongst HIV-positive women reported rates between 23.4 and 43.5% in the antenatal and 22.5 and 31% in the postnatal periods [3]. More recently, a global meta-analysis comparing rates of depression amongst HIV-positive and HIV-negative women in both the antenatal and postnatal periods, found that HIV-positive women had significantly higher odds of depressive symptoms [2]; 36% of HIV-positive women experienced antenatal depression compared to 26% of HIV-negative women, whilst 21% of HIV-positive women experienced postnatal depression compared to 16% of HIV-negative women. Given that up to a third of all women attending antenatal services in Southern Africa are HIV-positive, these differences are clinically important.

Perinatal depression may contribute both directly and indirectly to a wide range of maternal and child health risks [4, 5]. Studies show that perinatal depression amongst HIV-positive women is associated with increased suicidal ideation, with rates as high as 40% in some studies [3, 6]. Amongst HIV-positive women, perinatal depression has been associated with lower clinic attendance and poor adherence to antiretroviral treatment (ART) [7, 8]. A recent systematic review and meta-analysis estimated that, for people living in sub-Saharan Africa, depression approximately doubled the odds of non-adherence (OR 2.54 95% CI [1.7-3.9]) [9]. Psychological therapies, especially those using cognitive behavioural approaches have been shown to improve both depression and adherence to ART in the USA [10, 11], although more evidence is needed in African countries [12].

The potential impact of perinatal depression on parenting and child development is of major concern. Studies have consistently shown that perinatal depression is associated with negative effects on children’s cognitive, language, behavioural and emotional development as well as growth, including risks of stunting [5, 13]. The persistence of depression appears to be more likely to lead to negative effects on the child [14], highlighting the need for treatment. The quality of caregiving is a key mediator of the negative effects of parental depression on child development. An important reason for this is the effects of rumination, a core characteristic of cognition in depression, on responsiveness to a young child [15]. Rumination consists of recurrent negative thoughts that are intrusive and difficult to dismiss, absorb attention and are associated with reduced problem-solving, speed of response to external stimuli and disturbances in attention. This is important because focused maternal attention to the infant and contingent responsiveness to infant cues and behaviour is essential to early cognitive and emotional childhood development. Furthermore, depression disrupts the ability to scaffold and support an infant’s exploratory behaviour and emotional states, especially infant distress and this can disrupt emotional and behavioural development [5, 16].

Finally, maternal depression may affect child growth, gastrointestinal and respiratory infections, and general health through a shorter duration of exclusive breastfeeding (EBF) and lower rates of health and hygiene promoting behaviours [17, 18]. EBF is of particular importance in HIV-positive populations as studies have found that optimal early-life feeding practices ameliorate the effects of being born to an HIV-positive mother [19]. Furthermore, EBF has been shown to reduce episodes of diarrhoea in infants born to HIV-positive mothers [20].

Consequently, maternal depression in the context of HIV is associated with several maternal and child health risks. The combination of HIV and depression in the perinatal period is especially important because the negative impact of depression on children is amplified by socio-economic adversity and lack of support [4, 5], which are associated with HIV [21]. Thus, the clinical implications of perinatal depression amongst HIV-positive women are likely extensive in HIV-endemic regions.

These effects of depression in the context of HIV on child development forms part of a growing body of literature underscoring the importance of early-life exposures for long-term health and development [22–24]. As a result, international agencies, including the World Health Organization, are developing evidence-based policies and interventions aiming to improve early child development, encapsulated in the Nurturing Care Framework [25]. The Nurturing Care Framework has two guiding implementation features; firstly, to ensure the child receives multiple intervention inputs required to support healthy development, including adequate nutrition and health, early learning opportunities, safety and security and responsive care. Secondly, the framework attends to the enabling environment of care, including the mental health of caregivers and their support [24]. The present study is situated within this new scientific and policy focus.

#### Interventions for perinatal depression in LMIC

In recent years, task-shifting of mental health care services to trained lay health care workers has been strongly advocated for in an effort to increase treatment coverage for mental health disorders in LMICs [26, 27]. A range of intervention studies in LMICs have used task-shifting to community health workers (CHW) or lay counsellors to support women with perinatal depression. Internationally, such studies report that psychological treatment by peer or lay counsellors is feasible and generally has positive effects compared to routine standard of care [27]. A 2014 review of nine South African psycho-social interventions delivered by CHWs or lay counsellors (several of which targeted pregnant women) reported that the majority of studies provided evidence for the effectiveness of task-shifted interventions which include psychological content [28], although one recent RCT in South Africa for perinatal depression, not specifically targeting HIV-positive women, did not report significant effects on maternal mood [29].

There has been one example of a randomised controlled treatment trial (Masihambisane Trial) which tested the effectiveness of a clinic-based peer-mentor support intervention addressing health, including mental health, and stigma faced by perinatal HIV-positive women (not necessarily experiencing depression) in rural KwaZulu-Natal, South Africa. This study showed improvements in maternal mental health but also found that centre-based activities presented significant challenges to retention [30]. To our knowledge, only one published RCT in Africa has directly tested the effects of an intervention specifically for HIV-positive pregnant women on perinatal depressive symptoms (and prenatal disclosure rates of HIV). The trial compared a 6-week psycho-social support group facilitated by nursing staff with the standard of care (SoC) in Dar es Salam, Tanzania. The trial found that marginal non-significant improvements in the intervention arm compared to the SoC arm and there was a high attrition rate [31].

In addition to Kaaya et al. (2013) [31], other studies in LMICs have reported high attrition rates in clinic- and group-based studies exploring mental health interventions in HIV-positive populations. Petersen et al. reported an attrition rate higher than 45% in a randomised controlled pilot study of group-based interpersonal therapy intervention for depressed HIV-positive patients in South Africa [32]. The low uptake of the intervention was attributed to limited transport opportunities and money, employment responsibilities on treatment days and discomfort with the group approach (particularly gender and age similarities were cited as important for ensuring comfort in relaying sensitive issues). As mentioned above, the Masihambisane found low uptake of sessions in a clinic-based peer-mentor intervention for HIV-positive women in the perinatal period, citing opportunities and costs and clinic waiting times as significant barriers to clinic-based interventions [30]. In contrast, home-based interventions for HIV-positive women in South Africa have been documented to reach more than 98% of women and follow-up rates were more than 91% at 6 months [33]. Thus, in the present study, we planned to use a home-based individual intervention to overcome some of the barriers to clinic-based group interventions.

#### Interventions for parenting in LMIC

Parenting interventions that support caregivers and provide guidance on practices and skills that help caregivers to support their young child’s development have been beneficial in improving early childhood development (ECD) outcomes and reducing risks of developmental delay. The most recent global meta-analysis of parenting interventions, comprising 90 RCTs, found small (*β* = 0.19, socioemotional) to medium (*β* = 0.31–0.34, cognitive and language) effects on ECD. It is noteworthy that interventions that included strategies to support responsive caregiving had stronger effects on children’s development [34], however, there are evidence gaps. Firstly, only a small number of parenting interventions implemented in LMIC evaluated children’s early socioemotional development. Secondly, fewer interventions have assessed caregiver mental health. In a review that examined care outcomes for parenting interventions in LMIC, nine of the 15 interventions assessed maternal depressive symptoms and the meta-analyses did not report any significant reduction in depressive symptoms [35]. Parenting interventions that include components to promote mental health, rather than focusing only on the needs of the child, are likely to be beneficial for children and their caregivers [36]. More research is needed on how these interventions can be effectively combined and tailored to the needs of at-risk families.

To our knowledge, the present study is the first to test a home-based integrated intervention specifically targeting HIV-positive, perinatally depressed women, which combines treatment for depression with a parenting intervention delivered by lay counsellors.

#### The Insika Yomama intervention

In this trial, we test a novel integrated intervention to treat HIV-positive perinatally depressed women and enhance child development, using a combination and adaptation of two evidence-based interventions: (i) behavioural activation (BA) for depression and (ii) and the WHO/UNICEF Care for Child Development (CCD) package.

*Behavioural activation (BA)* is being trialled because it has been shown to be as effective as cognitive behavioural therapy (CBT) in high-income settings [37–39]. BA is easier to deliver than CBT since it does not require extensive training or complex counselling skills. Studies suggest that BA delivered by non-specialists appear similar to those with formal therapy qualifications [40]. Importantly, studies report that BA is effective in treating depression in LMIC when delivered by a range of non-specialist health care workers [41]. As a result, BA lends itself to task-shifting [42, 43]. In South Africa, the National Mental Health Policy Framework (2013–2020) acknowledges task-shifting as a critical approach to improving mental health nationally [44, 45]. Furthermore, BA is considered to be suitable for cross-cultural delivery because it targets behavioural change rather than beliefs and attitudes. To date, BA has not been tested amongst HIV-positive women in the perinatal period.

*The WHO/UNICEF CCD* package was developed to promote early childhood development, especially cognitive development, through responsive caregiving and early stimulation [46, 47]. Evaluations of CCD implementation have shown that the CCD strategy can be feasibly delivered by CHWs and there is good acceptability and demand from families [23, 48, 49]. Meta-analyses have shown significant benefits from programmes that support parents to enhance early stimulation as a means to improve early child cognitive development, including language development [50]. The CCD package has also been adapted and evaluated in several LMIC with positive results although it has not yet been tested in the context of perinatal depression or HIV, nor does it include content for pregnant women [50, 51]. Thus, the present trial is the first to adapt the CCD package for perinatally depressed, HIV-positive women. Furthermore, in this study, CCD has been augmented with specific content to begin during pregnancy including visual aids for lay counsellors, including information sheets and handouts.

### Objectives {7}

The primary objective is to test whether a home-based intervention, integrating behavioural activation for depression with a parenting programme adapted from CCD, for HIV-positive women with perinatal depression compared to Enhanced Standard of Care (ESoC) improves:
Maternal perinatal depression at 12 months postnatalChild cognitive development at 24 months of age

#### Secondary objectives:

To identify if the combined intervention compared to the ESoC:
Improves maternal depression at end of pregnancy^1^ and 24 months postnatal.Improves maternal anxiety at the end of pregnancy and 24 months postnatal.Increases maternal adherence to Antiretroviral Treatment (measured as viral load (VL) and viral suppression post-initiation of treatment) over the trial period.Increases rates of exclusive breastfeeding to six months postnatal.Improves adherence to infant immunisation schedule over the 24-month postnatal period.Reduces episodes of diarrhoea over the postnatal period^2^.Improve the quality of infants’ cognitive and emotional stimulation within the home environment at 12 and 24 months.Reduces child behavioural difficulties at 12 and 24 months postnatal.Improves child language development at 24 months postnatal.Improves child growth (infant height and weight) at 24 months postnatal.

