##### Secondary outcomes

The 10 secondary outcomes and the associated measures are summarised in Table 2 and Table 3.

**Table 2 Tab2:** Secondary outcomes

	Domain	Measure	Metric	Method of aggregation	Timepoint
1	Maternal depression	Edinburgh Postnatal Depression Scale (EPDS), total score	Mean difference	Mean and SD	End of pregnancy; 24 months postnatal
2	Maternal anxiety	Generalized Anxiety Disorder 7-item (GAD-7) scale, total score	Mean difference	Mean and SD	End of pregnancy, 24 months postnatal
3	Maternal antiretroviral treatment adherence	Viral Suppression (Yes/No)	Risk ratio	Frequency and percentage	End of pregnancy; 12 weeks, 12 months, 24 months postnatal
4	Exclusive breastfeeding	Exclusive breastfeeding at 6 months (Yes/No)	Risk ratio	Frequency and percentage	6 months postnatal
5	Adherence to infant immunisation schedule over the 24-month postnatal period	No. of immunisations recorded	Mean difference	Mean and SD	12 weeks, 12 months, 24 months postnatal
6	Infant diarrhoea	Any maternal report of diarrhoea over the previous 14 days.	Risk ratio	Frequency and percentage	12 weeks, 6 months, 12 months, 24 months postnatal
7	Cognitive and emotional stimulation within the home environment	Early Childhood Development section of Multiple Indicator Cluster Surveys (MICS6) Questionnaire for cognitive and emotional stimulation for children under five, total score	Mean difference	Mean and SD	12 months, 24 months postnatal
8	Infant behaviour	Parenting Stress Index, Short Form (PSI/SF: parent-child dysfunctional interaction subscale and difficult child subscale, total score	Mean difference	Mean and SD	12 months postnatal
		Externalising subscale of Child Behaviour Checklist (CBCL), total score	Mean difference	Mean and SD	24 months postnatal
9	Child language development	Language subscale of the Bayley Scales of Infant and Toddler Development III (BSID-III), Composite score	Mean difference	Mean and SD	24 months postnatal
10	Child growth (infant height and weight at 24 months)	Road to Health Book, study Weight and height measurements	Mean difference	Mean and SD	24 months postnatal

**Table 3 Tab3:** Mediators, including measures and timepoints

Mediators	Measure	
Family, relationship support and conflict	Relationship conflict questions adapted from the Romantic Partner Conflict Scale [59]. Support questions used from social support measure previously validated in South Africa [60].	Baseline, end of pregnancy, 12 weeks, 12 and 24 months

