**Secondary outcomes**										
EPDS	X			X			X			X
GAD-7		X		X					X	X
Maternal Antiretroviral treatment adherence		X		X			X		X	X
Exclusive Breastfeeding								X		
Infant immunisations							X		X	X
Infant diarrhoea							X	X	X	X
Cognitive and emotional stimulation (MICS)									X	X
Infant Behaviour (PSI/SF and Externalising subscale CBC)*									X	X
BSID-III language										X
Child Growth (weight and height)							X		X	X

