### Statistical methods

#### Statistical methods for primary and secondary outcomes {20a}

The primary inference will be based on the BSID-III cognitive score at 24 months and the EPDS at 12 months. For the primary outcomes and other continuous outcomes, the mean (SD) will be presented by the allocation group, and the mean difference (plus 95% confidence interval) will be estimated using mixed-effects linear regression. For binary outcomes, the number and percentage with the outcome will be presented by the allocation group, and the risk ratio (plus 95% confidence interval) will be estimated using a mixed-effect binomial or Poisson regression model.

The unit of randomisation is a geospatial cluster as outcomes are collected at the individual level, hence the unit of analysis is the mother and the infant. There is also an additional level of clustering by the counsellor delivering the intervention. The lack of independence amongst individuals in the same cluster and standard methods of analysis will underestimate the standard error of the treatment difference yielding *p* values that are too small. To account for the correlation of outcomes within clusters, the geospatial cluster and counsellor identifier will be fitted as random effects, with counsellor nested within the geospatial cluster. The intra-class correlation coefficients for geospatial cluster and counsellor will be estimated.

For the EPDS and the GAD-7, a repeated measures model will be fitted, including the baseline, end of pregnancy and 12-month and 24-month scores. For the cognitive and emotional stimulation at home outcomes, a repeated measures model will be fitted including the 12- and 24-month scores. Mixed-effects models with maximum-likelihood estimation allow participants with incomplete repeated measures data to be included in the model, contributing to the estimation of model parameters. The mean scores with 95% confidence intervals will be plotted over time by the allocation group.

In addition to adjusting for important baseline differences between randomised groups, any differences between participants followed up to 24 months and those lost to follow-up will be adjusted for in the final models. Both unadjusted and adjusted models will be fitted, but the primary inference will be based on the adjusted model which provides unbiased estimates if the outcome data is missing at random (i.e. only dependent on observed characteristics).

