#### Methods in analysis to handle protocol non-adherence and any statistical methods to handle missing data {20c}

Women with outcome data will be analysed in the groups to which they are randomly assigned, regardless of deviation from the protocol or treatment received (modified ITT population). Women whose infant died during the trial will also be included unless they withdrew consent to participate further in the trial.

The number and percentage of individuals missing data for outcome measurements that are based on summing items to give overall scores (e.g. EPDS, GAD-7, and subscales of the PSI/SF and CBCL) will be described. Missing items will be imputed if ≤ 20% are missing using the median score of completed scale items unless alternative guidance is provided in the scoring manual.

A multiple imputation analysis will be performed for the primary infant and maternal outcome if attrition exceeds 5%. The multiple imputation model will include baseline characteristics and outcome measures collected before the missing assessment, which are associated with missing status.

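### Child growth is scheduled at 12 weeks, 12 months and 24 months but left out of the repeated-measures models, so precision is lost and the 24-month contrast can be biased if growth-related loss differs by arm

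*Protocol article*

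**What the plan says.** **Target.** Under Secondary objectives, the growth objective is "Improves child growth (infant height and weight) at 24 months postnatal". Table 2, outcome 10, agrees: "Child growth (infant height and weight at 24 months", reported as a mean difference at 24 months.

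**Schedule.** The row "Child Growth (weight and height" in Table 4 carries marks at 12 weeks (A4), 12 months (A6) and 24 months (A7).

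**Model.** Section {20a} gives a general rule and then two lists of exceptions:
- General rule: "For the primary outcomes and other continuous outcomes, the mean (SD) will be presented by the allocation group", with the difference taken from a mixed-effects linear regression.
- First exception: "For the EPDS and the GAD-7, a repeated measures model will be fitted, including the baseline, end of pregnancy and 12-month and 24-month scores".
- Second exception: "For the cognitive and emotional stimulation at home outcomes, a repeated measures model will be fitted including the 12- and 24-month scores".

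Growth is in neither exception. The reason {20a} gives for such models is that they "allow participants with incomplete repeated measures data to be included in the model".

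**Missing data.** Section {20c} sets the analysis population: "Women with outcome data will be analysed in the groups to which they are randomly assigned". Multiple imputation is planned for the primary infant and maternal outcomes only, once attrition exceeds 5%. Section {20a} also says that differences between participants followed to 24 months and those lost will be adjusted for in the final models.

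**The concern.** Read together, these sections make growth a single-visit comparison among children measured at 24 months. A child weighed and measured at 12 weeks and 12 months and then lost contributes nothing, although earlier size carries information about the missing value. Home stimulation, with two scheduled measurements, gets a model that keeps such children; growth, with three, does not.

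Two things are at stake. The first is precision, because the 24-month visit is the last and the sample size allows for up to 25% attrition. The second is protection against selective loss. If children who leave differ in earlier growth, and differ in one arm more than in the other, those remaining at 24 months are no longer comparable between arms. A model that also contains the earlier values would correct this under missing at random.

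**Working it through.** **The plan's own figure.** The sample size section gives 396 evaluable women (198 per arm) and up to 25% attrition: 396 / (1 − 0.25) = 528, as stated (264 per arm). At that ceiling, 528 − 396 = 132 children have no 24-month value.

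**Inputs the documents do not give (assumed).**
- Children measured at 12 months, n₁₂: 85–95% of 264, about 224 to 250 per arm; central value 237 (90%).
- Correlation r between 12-month and 24-month growth: 0.6 to 0.9; central value 0.8.
- Growth is in SD units. The 12-week value is left out of the arithmetic.

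**Precision, clustering ignored.** With 198 seen at 24 months, the variance of an arm mean in units of σ² is 1/198 for the 24-month-only analysis. It is (1 − r²)/198 + r²/n₁₂ when the 12-month value is also used. The ratio is 1 − r²(1 − 198/n₁₂).

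| n₁₂ | r | Ratio | Variance cut | Equivalent n (198/ratio) |
|---|---|---|---|---|
| 224 | 0.6 | 1 − 0.36 × 0.116 = 0.958 | 4% | 207 |
| 237 | 0.8 | 1 − 0.64 × 0.165 = 0.895 | 10.5% | 221 |
| 250 | 0.9 | 1 − 0.81 × 0.208 = 0.832 | 17% | 238 |

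**Precision, with geospatial clustering.** Take the sample size section's 28 clusters per arm and ICC of 0.05. These are stated for the BSID-III and assumed here for growth. The between-cluster part, 0.05/28 = 0.00179, is unchanged by the earlier visit. Only the within-cluster part, 0.95/198 = 0.00480, shrinks by the ratio above. The 24-month-only total is 0.00658.
- Low: (0.00179 + 0.00480 × 0.958) / 0.00658 = 0.969, a 3% cut.
- Central: (0.00179 + 0.00480 × 0.895) / 0.00658 = 0.923, a 7.7% cut, or about 4% off the standard error.
- High: (0.00179 + 0.00480 × 0.832) / 0.00658 = 0.877, a 12% cut.

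Adding four counsellors with ICC 0.05 in the intervention arm, treated approximately as crossing clusters, adds 0.05/4 = 0.0125 to that arm's variance. The cut is then about 2–6%, centrally 4%.

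**Bias.** Large simulated arms, no true effect, 75% observed at 24 months, r = 0.8, loss depending on 12-month growth with the log-odds slope shown:

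| Slope per SD (arm A / arm B) | 24-month-only contrast | Using the 12-month value |
|---|---|---|
| 0 / 0.3 | off by 0.06 SD | 0.00 |
| 0 / 0.5 | off by 0.10 SD | 0.00 |
| 0.3 / 0.3 or 0.5 / 0.5 | about 0 | 0.00 |

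A second set of runs used a stronger slope of 0.7, correlations of 0.5–0.8 and a true 24-month difference of 0.20 SD. With the same slope in both arms, the 24-month-only estimate was about 0.20, or 0.19 when there was also an effect at 12 months. With the slope in the control arm only, it fell to 0.07–0.12. The analysis using the earlier value gave 0.20 throughout.

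**The case against.** **Nothing in the article is contradictory.** The objective and Table 2 agree on 24 months, and fixing one time point for a secondary outcome is legitimate. This stands: the target should stay.

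**Silence in a condensed article is not exclusion.** The article says that a statistical analysis plan will be made available; it is not shown and may add a longitudinal growth model. But {20a} does not leave the matter open. It lists which outcomes and visits enter repeated-measures models and puts other continuous outcomes under the general rule. The point is an improvement on a stated choice, not a complaint about missing detail.

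**The plan addresses selective loss.** The adjustment in {20a} for followed-versus-lost differences is relevant, but only a partial answer. It does not bring lost children into a single-visit model and does not name earlier growth. Entering 12-month growth as a covariate would condition on a post-randomisation value and could remove part of the treatment effect.

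**Bias is conditional.** A reader might infer that any drop-out related to earlier growth biases the contrast. The documents do not support that: the calculation gives little or no bias when the relation is the same in both arms, and both arms share the assessment schedule and tracing procedures. Loss that differs by arm remains possible. Eligibility requires residence only to 9 months postnatal, the 24-month assessment moves from home to clinic, and contact differs: intervention sessions run to 9 months with a booster at 16 months, while ESoC calls end at 4 months. That makes it conceivable, not shown.

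**The gain is modest.** This stands. Clustering shrinks it, the 25% is a ceiling, and at r = 0.6 the 12-month value explains only 36% of the variance. Children lost before 12 weeks contribute no growth data under either analysis. Neither primary outcome is affected.

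**Conclusion.** The point holds as a minor improvement. As written, the growth analysis uses only children seen at 24 months and ignores two earlier scheduled measurements. {20a} gives its own reason for handling other repeated outcomes differently, and that reason applies equally here.

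Under the assumed follow-up and correlations, the cost is about 4–17% of the variance ignoring clustering, 3–12% with the geospatial ICC, and less again with counsellor clustering. The bias of 0.06–0.10 SD arises only if loss depends on growth in one arm and not the other, at the assumed slopes and r = 0.8. The text does not show that such loss will occur, nor that choosing 24 months was a mistake.

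**What to change.** In {20a}, add child weight and height to the outcomes with a repeated-measures model. Use the 12-week, 12-month and 24-month values, arm-by-visit terms, and the same clustering terms as the other outcomes. State that the 24-month difference remains the secondary-outcome estimate; a separate 12-month contrast is not needed. In {20c}, note that children with any scheduled growth value enter this model.

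The cost is analysis wording and a slightly more complex model for one secondary outcome. Table 4 already schedules the measurements, so no visits or participants are added. If the analysis plan already contains such a model, a sentence in {20a} pointing to it is enough.
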